### Intervention

Following baseline measures, the intervention group will receive an introduction to the downloading process and a demonstration of the app [28,36-39]. They will also be provided with a user’s manual and 2 resistance bands with a resistance of their choice (TheraBand, The Hygenic Corporation), one of which is for backup. The intervention group will perform a 6-week home-based exercise program delivered by the ParaGym mobile exercise app, comprising three 35-minute exercise sessions per week. The app offers a different workout every day, and participants get to choose the days on which they want to exercise. An exercise session consists of 4 parts: warm-up, 2 exercise parts, and cooldown. The first exercise part focuses on the correct execution of the exercises at a moderate intensity and prepares the musculature for the high-intensity second part. Exercise sessions aim at various training goals, such as stabilization of the shoulder girdle and improvement of wheelchair mobility. The waitlist control group will only maintain usual care and receive access to the mobile app after postintervention measurements.

### Measures

#### Primary Outcomes

##### Overview

The primary outcomes are feasibility, usability, and safety. Six weeks after commencing the intervention, semistructured interviews will be conducted via phone to investigate feasibility and usability. An interview guide was conceptualized based on interview domains and topics in similar studies [27,36,39-43]. The following topics will be addressed: (1) overall experience, (2) ease of use, (3) app functionality, (4) perceived safety, (5) technical functionality, (6) communication, (7) perceived effects and usefulness, (8) adherence and motivation, and (9) recommendation. The interviews will be audio recorded with the consent of the participants.

##### Feasibility

During their first site visit, participants in both the intervention and waitlist control groups will be provided with an exercise diary (Multimedia Appendix 2). They will be asked to record the following: (1) any physical activities, including app exercise sessions, additional exercise sessions (eg, hand biking), and physical therapy; (2) the time spent performing the exercise; (3) the intensity of the exercise; and (4) any annotations concerning the exercise sessions as needed (eg, whether the session adapted by the algorithm was appropriate in terms of the choice of exercise and intensity). This will help obtain more information about the feasibility of the app in addition to the information provided in the retrospective interviews and help assess adherence to the program. Adherence rates in terms of completed sessions will also be measured based on app use data. Furthermore, retention rates will be measured by assessing dropout rates and reasons. As both adherence and retention are study outcomes, they should not be influenced by the investigators. Therefore, no measures will be taken to promote either of them. All outcome measures will be obtained regardless of adherence.

##### Usability

The SUS [44] is a 10-item Likert scale ranging from 1 (“strongly disagree”) to 5 (“strongly agree”) and is a common tool for investigating the usability of health-related mobile apps [27,36,38,39,41-43,45,46]. The score will be converted according to Brooke [44], so the total score will range from 0 to 100. The app will be considered usable if the overall SUS score is at least 70 [47].

##### Safety

The safety of the app-based exercise program will be determined based on the occurrence of intervention-related AEs and SAEs. Participants will be instructed to report any AEs or health-related interruption of the intervention within 24 hours. AEs and SAEs will be classified by the grade of severity based on the Spinal Adverse Events Severity System version 2 (SAVES-V2) scale [48] (Table 2) and expectance. The following AEs and SAEs can occur because of physical strain or are common complications after SCI and are, therefore, classified as expected AEs or SAEs: (1) autonomic dysreflexia, (2) pressure ulcers, and (3) shoulder pain [49].

**Table 2 table2:** Classification of adverse events (AEs) and serious adverse events (SAEs) based on the Spinal Adverse Events Severity System version 2 scale.

Severity of AE or SAE	Clinical impact
1	AE—no treatment
2	AE—outpatient treatment
3	SAE—inpatient treatment
4	SAE—life-threatening injury
5	SAE—death

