### Development of the ParaGym Mobile Exercise App Prototype

The development of the ParaGym mobile exercise app prototype is based on the Kernwerk mobile exercise app (Kernwerk GmbH), which was designed to improve general fitness in able-bodied individuals. The Kernwerk app offers daily functional training sessions created by exercise scientists and uses an intelligent algorithm to individualize these sessions to the user’s needs. The goal of the ParaGym project is to develop a prototype of an intelligent mobile exercise app for individuals with paraplegia.

The ParaGym mobile exercise app uses the same algorithm to provide an automatically individualized training program for people with paraplegia. The steps taken to develop the app are as follows. A user-centered approach was adopted to create the ParaGym exercise app for people with paraplegia. This included a survey among the target group and an extensive review of the literature [32] to identify both health-related and disability-related demands for an exercise program and a mobile fitness app. The results of the survey and the literature review revealed the following: (1) there is an urgent need for accessible and personalized exercise programs; (2) exercises with free weights are preferred over exercises with machines; (3) the exercise pool should contain stretching exercises and exercises to improve scapula coordination; (4) workouts should focus on the dorsal rather than the ventral shoulder musculature to avoid overuse injuries; and (5) users should be provided with comprehensive information about the potential risks of exercising (eg, increased risk of autonomic dysreflexia) and, if required, be cleared by a physician.

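### Table 2 gives no route by which lasting disability makes an event serious, so a disabling injury managed without admission is classed as a non-serious AE

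*Protocol article*

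**What the plan says.** The Safety section, under Primary Outcomes, states the basis of the safety conclusion: "The safety of the app-based exercise program will be determined based on the occurrence of intervention-related AEs and SAEs". Events are sorted on two axes.

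- **Severity.** The section says "AEs and SAEs will be classified by the grade of severity based on the Spinal Adverse Events Severity System version 2". Table 2 prints five classes. Grade 1 is "AE—no treatment", grade 2 is "AE—outpatient treatment", grade 3 is "SAE—inpatient treatment", grade 4 is "SAE—life-threatening injury", and grade 5 is an SAE ending in death. The grade thus carries the AE or SAE label with it.
- **Expectedness.** Three events count as expected, listed as "1) autonomic dysreflexia, (2) pressure ulcers, and (3) shoulder pain".

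The Quantitative Analysis section assesses safety by comparing the number of study-related AEs or SAEs between the intervention and waitlist groups. It sets no safety threshold, whereas adherence (66%) and retention (75%) have one there and the SUS (70) has one in the Usability section.

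**The concern.** Severity and seriousness are separate properties of an event, and Table 2 merges them into one scale. The lowest serious grade is reached by admission. The two above it are reached by threat to life or by death. Duration and functional consequence appear nowhere.

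This matters for this population. Two of the three expected events, shoulder pain and pressure ulcers, can be handled without admission, and both can impair transfers and propulsion in people who rely on their arms. The Secondary Outcomes overview treats independence as central to rehabilitation after spinal cord injury, and the Independence section names transfers among the activities that the SCIM III covers. The trial therefore counts function as a benefit but leaves its loss out of the definition of serious harm.

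What is at stake is the summary statement on SAEs. The Discussion expects the program to be safe, and the Conclusions and Implications look ahead to a full-scale trial in a broader group. A report of no SAEs would be read in that light.

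**Working it through.** The plan gives no figure for this point, so the check is to run the case through the printed rule.

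**Test case.** A shoulder injury or pressure ulcer judged related to the intervention, with lasting loss of independent transfers, not admitted, not life-threatening, not fatal.

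| Table 2 class | What puts an event there | Test case |
|---|---|---|
| 5, SAE | death | no |
| 4, SAE | threat to life | no |
| 3, SAE | inpatient treatment | no |
| 2, AE | outpatient treatment | yes, if treated |
| 1, AE | no treatment | yes, if untreated |

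The event is grade 1 or 2 and non-serious. If recorded as shoulder pain or a pressure ulcer, it is also expected.

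**Is there another route to seriousness?** None appears in the article. The second axis, expectedness, does not alter the AE or SAE label. The SCIM III is measured at t0 and t1, but as a secondary effectiveness outcome with no link to event grading.

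**What changes and what does not.** The comparison in Quantitative Analysis counts AEs or SAEs together. The test case adds one to that count whether labelled AE or SAE. Only the SAE tally differs: 0 under Table 2 as printed, 1 with a disability criterion.

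**Illustration of the SAE tally.** This assumes one such event and no other SAE. The denominator is also assumed. GSU randomizes 30 participants 1:1, giving 30/2 = 15 app users. The 15 Tübingen participants are not randomized, and if all use the app the total is 15 + 15 = 30. With exact (Clopper-Pearson) two-sided 95% limits, the upper limit for 0/n is 1 − 0.025^(1/n). For 1/n, the limits are the 2.5% quantile of Beta(1, n) and the 97.5% quantile of Beta(2, n − 1).

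| App users | SAE tally 0 | SAE tally 1 |
|---|---|---|
| 30 | 0%, upper limit 11.6% | 3.3% (0.1% to 17.2%) |
| 15 (GSU only) | 0%, upper limit 21.8% | 6.7% (0.2% to 31.9%) |

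The intervals overlap heavily. The difference is between reporting no SAE and reporting one, not a measurable shift in risk.

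**The case against.** The strongest reply is that nothing planned turns on the SAE count alone. Safety rests on AEs and SAEs together, there is no threshold, and the event would still be reported, graded and, if judged related, counted. **This stands**, and it limits the point to labelling.

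Second, the loss of function would probably be seen. The SCIM III is taken at both visits, reasons for dropout are recorded, health-related interruptions must be reported within 24 hours, and app users are interviewed about perceived safety. **This stands in part.** These sources may show the loss, but none changes the class of the event.

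Third, the authors adopted a cited spinal-specific scale, so a further criterion could be called a preference. **This does not remove the point.** The article prints a complete rule, and that rule gives a misleading class in a primary outcome. Nothing here depends on what the source publication of the scale contains, which was not available.

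Three stronger readings are tempting but unsupported:

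- A reader might infer that treatment setting alone decides seriousness. It decides only the boundary between grades 2 and 3. Grades 4 and 5 rest on threat to life and death.
- A reader might take overuse injury to be a harm that the plan expects, because the app development section says "workouts should focus on the dorsal rather than the ventral shoulder musculature to avoid overuse injuries". That sentence reports a survey and literature result used to design the workouts. Overuse injury is not on the list of expected events.
- A reader might infer that the disabling event disappears from the safety analysis. It does not.

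**Conclusion.** The point holds in a limited form. On the article's only definition of seriousness, an intervention-related event with persistent or significant disability is non-serious unless it also leads to admission, threatens life or kills. The planned AE-or-SAE comparison is unaffected, but a statement that no SAEs occurred could coexist with a disabling event.

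The size is one label per such event. The figures in the illustration rest on a hypothetical event and an assumed denominator of 15 to 30, and should not be read as an estimate of risk. The conclusion assumes that no fuller protocol or event form overrides Table 2 with a separate definition of seriousness. The article does not mention one. This is a minor, cheap improvement and does not threaten the validity of the trial.

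**What to change.** - Keep the SAVES-V2-based grade as the severity measure.
- In the Safety section and Table 2, define seriousness separately. Retain the present criteria (inpatient treatment, threat to life, death) and add persistent or significant disability or incapacity, whatever the treatment setting. Lost independent transfers or wheelchair propulsion would serve as examples.
- Do not make an event serious merely because it is unresolved at t1. With t1 following a 6-week program, mild shoulder pain that began in the last week would qualify, and the SAE class would lose meaning.
- Report severity grade and seriousness separately, by group.

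The cost is a short addition to the text and table and one more column in the safety report. Treatment, visits and sample size are unchanged. The drawback is that a few more events may be labelled serious, and deciding whether a disability is significant needs some judgement.

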	**Safety**									
		Adverse events					✓			
		Serious adverse events					✓			

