### Study Design

This pilot mixed methods block-randomized controlled feasibility trial with an allocation ratio of 1:1 for the intervention and waitlist control groups is conducted at the German Sport University Cologne (GSU), Germany. The trial was registered with the German Clinical Trials Register (DRKS00030370).

Participants will be recruited at the GSU and the SCI center at the BG (*Berufsgenossenschaft*; English: occupational insurance association) clinic Tübingen, Germany. Participants will be recruited at the GSU via the project newsletter, the project website, social media, and by contacting rehabilitation centers and spinal cord associations. The BG clinic in Tübingen will recruit among their patients.

Measurements will be conducted at baseline (t_0_) and after the intervention (t_1_; Table 1). The primary outcomes (feasibility, usability, and safety) will be assessed during the intervention and at t_1_. The secondary outcomes (peak exercise capacity, handgrip strength, independence, and quality of life) will be assessed at t_0_ and t_1_. As data collection at the BG clinic Tübingen will focus on the primary outcomes and owing to limited capacity, the ramp exercise test for evaluating peak exercise capacity and handgrip strength test will be conducted only at the GSU and not at the BG clinic Tübingen. After randomization and group allocation, participants in the intervention group will be provided with the ParaGym mobile exercise app and uptake a 6-week home-based training intervention. The participants will be instructed to complete 3 training sessions per week. For this cohort, resistance training for at least 2 days a week is recommended [2,6]. As the training sessions delivered by the app comprise not only strength but also aerobic and flexibility exercises, we decided to provide training sessions for 3 days instead of 2. Eitivipart et al [34] recommend 3 sessions for a minimum duration of 20 minutes per week over at least 6 weeks to achieve substantial outcomes. The waitlist control group will proceed with their usual care and receive access to the mobile app once they have completed the trial. After the 6-week intervention, participants in the intervention group will be interviewed over the phone to assess feasibility and usability. Subsequently, both groups will return to the study site (t_1_) for the SUS questionnaire and secondary outcome measures. The study design and planned participant flow are presented in Figure 3.

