### Participants

#### Eligibility Criteria

Participants are eligible for the study if they meet the following inclusion criteria: (1) chronic paraplegia (time since injury >1 year), (2) age between 18 and 67 years, (3) sufficient German language skills, (4) ability to provide informed consent, and (5) access to a smartphone. Participants will be excluded from the trial if they have any of the following conditions or diseases: (1) acute infection or inflammation (eg, urinary tract infection or pressure ulcers), (2) uncontrolled hypertension or diabetes, (3) manifest cardiovascular diseases, (4) psychiatric or mental conditions that compromise informed consent or may interfere with the study results (eg, major depression and psychotic disorders), (5) ongoing alcohol or substance abuse, and (6) other medical contraindications. In addition, they will be excluded if they are high-performance athletes (in the national team).

Potential participants will be enrolled based on the results of the medical screening using their medical records, a resting electrocardiogram, and the Physical Activity Readiness Questionnaire for Everyone (PAR-Q+) [35]. Because participants recruited by the BG clinic Tübingen will not perform exercise tests, a resting electrocardiogram is not required.

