#### Quantitative Analysis

Quantitative data analysis will be performed using SPSS. All data will be tested for normal distribution using the Shapiro-Wilk test. Study participant characteristics will be presented descriptively by calculating means and SDs for normally distributed variables. Median values and IQR will be calculated for skewed continuous variables, and absolute and relative frequencies will be calculated for nominal variables. Group differences at baseline will be calculated for independent samples using a 2-tailed *t* test, Mann-Whitney *U* test, or chi-square test depending on the distribution and level of measurement. At t_1_, normally distributed continuous variables will be analyzed using a mixed analysis of variance model to test for significant effects for group and time. For skewed continuous variables, Wilcoxon and Mann-Whitney *U* tests will be conducted to test the differences between the groups and between t_0_ and t_1_. The significance level will be set at *P*<.05. Absolute and relative frequencies will be reported for adherence and retention.

Feasibility will be assumed if (1) at least 66% of the training sessions (equivalent to 2 out of 3 sessions per week) are completed [43] and (2) the retention rate is at least 75% [67]. Exercise diaries will be analyzed in terms of the frequency, duration, and intensity of the training sessions. Safety will be assessed by comparing the number of study-related AEs or SAEs in the intervention group with that in the waitlist control group [68].

Spearman correlations will be used to assess the association between performance and strength outcomes and SCIM III and SF-36 outcomes. Subgroup analyses might be conducted for lesion level (high vs low paraplegia) and age. Missing data will not be imputed.

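### Adverse events come from participant-initiated reports, with no scheduled baseline for shoulder pain or dysreflexia and extra elicitation in the app arm only, so background problems cannot reliably be separated from programme harm

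*Protocol article*

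**What the plan says.** - **Endpoint.** Under Safety, the protocol states that safety "will be determined based on the occurrence of intervention-related AEs and SAEs". Under Quantitative Analysis: "Safety will be assessed by comparing the number of study-related AEs or SAEs in the intervention group with that in the waitlist control group".
- **Expected events.** Autonomic dysreflexia, pressure ulcers and shoulder pain "can occur because of physical strain or are common complications after SCI and are, therefore, classified as expected AEs or SAEs".
- **Capture.** "Participants will be instructed to report any AEs or health-related interruption of the intervention within 24 hours". No other route for collecting events is described.
- **Schedule.** In Table 1, adverse events and "Serious adverse events" are ticked in the postallocation period only. The baseline characteristics listed are demographics, lesion level, lesion completeness, time since injury and anthropometrics. No item at t0 or t1 is specific to shoulder pain or dysreflexia.
- **Entry.** Eligibility Criteria require an injury more than one year old. Pressure ulcers are an example under the exclusion for acute infection or inflammation, and screening uses medical records and the PAR-Q+. Shoulder pain and a history of dysreflexia are not named exclusions.
- **Interview.** Under Study Design, "participants in the intervention group will be interviewed over the phone to assess feasibility and usability". Perceived safety is one of the nine interview topics.

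**The concern.** The endpoint requires each event to be attributed. By the protocol's own account the three expected events have two possible origins: strain, which the programme may cause, and the underlying condition. Someone years after injury may enter with shoulder pain or recurrent dysreflexia. Without a recorded starting level, the assessor cannot say whether a report in week 3 is new, worse or unchanged. Chronic pain may then be counted as harm, or a real worsening put down to the condition.

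The second strand is unequal elicitation. Participants know their arm, since one group receives the app and the other waits. App users have one reporting trigger that controls cannot meet, an interruption of the intervention, and they alone have a closing conversation in which safety is raised. If opportunities to mention an event differ by arm, a difference in counts may reflect who was asked.

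**Working it through.** The protocol states no adverse event rate, power or formula-based sample size for safety, so there is no figure to reproduce. The check compares the passages and adds an illustration on stated assumptions.

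**1. What each arm is offered**

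| Route | App arm | Waitlist arm |
|---|---|---|
| Instruction to report any AE within 24 hours | yes | yes |
| Trigger: health-related interruption of the intervention | yes | cannot apply |
| Exercise diary (activity, time, intensity, notes on sessions) | yes | yes, no symptom field described |
| Phone interview including perceived safety | yes | no |
| Scheduled shoulder pain or dysreflexia item at t0 and t1 | none listed | none listed |

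**2. Starting status of the three expected events**

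Active pressure ulcers are looked for at entry through the exclusion criterion. For shoulder pain, dysreflexia and a history of relapsing ulcers, neither the schedule nor the exclusions give a recorded starting point.

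**3. What the waitlist arm can supply**

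Inputs: 30 participants randomised 1:1 at the German Sport University Cologne (Randomization; Study Design), so 30 / 2 = 15 per arm. The 15 participants at Tübingen are not randomised.

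Assumption: a background risk p of 10% to 50% over six weeks of at least one reportable expected event.

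- Expected participants with an event, no harm: 15 × p, from 15 × 0.10 = 1.5 to 15 × 0.50 = 7.5 in each arm.
- Power to detect a true excess of 20 percentage points (two-sided 5%, n = 15 per arm), with p1 = p + 0.20, p2 = p and p̄ their mean: Φ{[0.20 − 1.96·√(2p̄(1 − p̄)/n)] / √([p1(1 − p1) + p2(1 − p2)]/n)}.

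For p = 0.10: p̄ = 0.20, [0.20 − 1.96 × 0.1461] / 0.1414 = −0.61, and Φ(−0.61) = 0.27.

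| Assumed background p | Expected per 15 | Power, normal approx. | Power, Fisher exact |
|---|---|---|---|
| 0.10 | 1.5 | 0.271 | 0.149 |
| 0.20 | 3.0 | 0.217 | 0.112 |
| 0.30 | 4.5 | 0.195 | 0.097 |
| 0.40 | 6.0 | 0.189 | 0.095 |
| 0.50 | 7.5 | 0.195 | 0.097 |

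The protocol names no test for adverse events. Power is used here only to express how imprecise the comparison is.

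**4. What unequal reporting can do**

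Assume no true harm, full reporting by app users and half reporting by controls. Expected counts are 15p against 7.5p: 1.5 against 0.75 at p = 0.10, and 7.5 against 3.75 at p = 0.50. The ratio is 2 whatever p is. Randomisation balances the true background in expectation, but it leaves this ratio untouched.

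**The case against.** The strongest reply is that much of this is absence in a condensed article. Screening and event forms may record more than is printed, and the randomised waitlist comparison is the proper tool for separating background from harm. Much of that stands, and it rules out several stronger readings:

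- A reader might infer that none of the three events has any baseline. The documents do not support this: active pressure ulcers are screened out, and records and the PAR-Q+ are reviewed.
- A reader might infer that background cannot be told from harm at all. The waitlist arm does give a group-level background rate. Its imprecision is partly the ordinary limit of a pilot, and the article acknowledges its small sample; added questions will not remove that.
- A reader might infer that controls are not asked to report. The instruction covers participants in general and any AE. A health problem that interrupts the programme would usually be an AE anyway, so the extra trigger alone is a modest asymmetry.
- A reader might infer that expected events are discounted. The protocol uses the label only to classify them.
- A reader might infer that interview statements inflate the count. No section says they enter it, and none says they are kept out.

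The Discussion also expects few adverse events, citing earlier exercise trials in this population, which argues for the low end of any background range.

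What the reply does not reach is the printed text itself. The schedule is set out item by item, and the app-only interview and trigger are stated features of the design. A group-level comparison also does not help to classify one participant's event, which the endpoint requires.

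**Conclusion.** The point holds in a limited form. For shoulder pain, dysreflexia and relapsing ulcers, the stated capture method cannot reliably separate pre-existing or recurring problems from programme harm, and the two arms do not have equal opportunity to report. The waitlist arm mitigates this only in part: on assumed background risks of 10% to 50%, power for a 20-point excess at 15 per arm is about 10% to 15% (Fisher exact) or 19% to 27% (normal approximation).

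The size of any bias is unknown. The twofold ratio above follows directly from the assumed half reporting by controls. It shows what unequal elicitation could do and is not an estimate. If the unprinted forms already hold a baseline symptom record, the first strand weakens; the unequal elicitation remains. Because safety is a primary outcome and the remedy is cheap, the change is worth making.

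**What to change.** In the Safety section and in Table 1:

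1. Add one short check covering shoulder pain, pressure ulcer and episodes of autonomic dysreflexia, worded identically, at t0 and t1 for every participant in both arms and at both sites.
2. Flag an expected event as treatment-emergent when it is new or worse than at t0.
3. Keep the 24-hour reporting as it is.
4. Under Quantitative Analysis, base the between-arm comparison on events captured by methods common to both arms, and report events known only from the interview separately.

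The cost is a few questions at visits already planned, plus a protocol and form amendment. There are two downsides. Prompted questions will raise event counts in both arms. Participants already past t0 will need retrospective baseline answers, which carry recall error and should be flagged as such. Treatment and sample size do not change.
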